## Abstract

**Background:**

In contrast with the recommendations of clinical practice guidelines, the most common treatment for anxiety and depressive disorders in primary care is pharmacological. The aim of this study is to assess the efficacy of a cognitive-behavioural psychological intervention, delivered by primary care psychologists in patients with mixed anxiety-depressive disorder compared to usual care.

**Methods/Design:**

This is an open-label, multicentre, randomized, and controlled study with two parallel groups. A random sample of 246 patients will be recruited with mild-to-moderate mixed anxiety-depressive disorder, from the target population on the lists of 41 primary care doctors. Patients will be randomly assigned to the intervention group, who will receive standardised cognitive-behavioural therapy delivered by psychologists together with usual care, or to a control group, who will receive usual care alone.

The cognitive-behavioural therapy intervention is composed of eight individual 60-minute face-to face sessions conducted in eight consecutive weeks. A follow-up session will be conducted over the telephone, for reinforcement or referral as appropriate, 6 months after the intervention, as required.

The primary outcome variable will be the change in scores on the Short Form-36 General Health Survey. We will also measure the change in the frequency and intensity of anxiety symptoms (State-Trait Anxiety Inventory) and depression (Beck Depression Inventory) at baseline, and 3, 6 and 12 months later. Additionally, we will collect information on the use of drugs and health care services.

**Discussion:**

The aim of this study is to assess the efficacy of a primary care-based cognitive-behavioural psychological intervention in patients with mixed anxiety-depressive disorder. The international scientific evidence has demonstrated the need for psychologists in primary care. However, given the differences between health policies and health services, it is important to test the effect of these psychological interventions in our geographical setting.

**Trial registration:**

NCT01907035 (July 22, 2013).

## Background

The prevalence of mental disorders in primary care (PC) in Europe is around 20-55% [1-3]. In association with the current economic crisis, there has been an alarming increase of PC consultations for psychological distress [4,5]. It has been estimated that a quarter of patients who attend PC consultations have had a mental disorder in the previous year, in particular problems related to anxiety and/or depression [1,2,6,7]. In our multi-tiered public health system, around 85-90% of these patients are treated in PC settings [8].

Among mood disorders, the coexistence of anxiety and depression is the norm rather than the exception [9]. Specifically, adjustment disorders are very common, that is, signs and symptoms of mixed anxiety/depression in the context of changing situations that force people to adjust to new situations [1,10].

Clinical practice guidelines recommend cognitive-behavioural therapy (CBT) as the treatment of choice for affective and mood disorders. The use of psychoactive drugs is only recommended for the most severe cases and always in combination with psychological treatment [11-14]. However, the real adherence to these evidence-based clinical guidelines is very poor in general, and several studies have shown that in PC psychoactive drugs are more widely used than psychological techniques, [15]. In relation of this, the Strategy for Mental Health of the Spanish National Health Service recognised that that there has been a significant medicalization of everyday life and that there is a tendency towards an overuse of pharmacological approaches, these requiring less time, as well as less professional expertise and involvement, for the treatment of disorders that should be addressed with specific psychological interventions [16].

There is strong evidence that the efficacy of psychological therapy and CBT in particular, is the same as or greater than pharmacological treatments of the most common affective and anxiety disorders, as well as it having greater long-term effectiveness [17-19]. Notably, the benefits of psychological approaches include a reduction in symptoms associated with anxiety and depression, a decrease in the risk of relapses, the stability of the effect of the treatment in the long term, and high rates of recovery, preventing the condition becoming chronic and decreasing healthcare costs, in terms of medical consultations and use of drugs, as well as sick leave [20-22]. Various studies have suggested that the introduction of psychological interventions in primary care may significantly reduce healthcare and social costs related to mental disorders [23,24]. Specifically, although the cost of psychological treatments may seem high due to the need for trained psychologists, psychological interventions, and CBT in particular, have been found to be more cost-effective in the long term compared to the cumulative costs of the use of antidepressants [25].

The introduction of this type of therapy in routine primary care practice may not be feasible due to, among other reasons, the limited time available per consultation. Some authors have suggested that the role of non-specialist psychologist (although trained in health psychology) should be included in primary care services [26,27]. The objective of this study is to assess the efficacy of CBT-based psychological interventions delivered by primary care psychologists in patients with mixed anxiety-depressive disorder.

### Aims of the study

The primary objective of this study is to assess the efficacy of a CBT-based psychological intervention delivered by psychologists in collaboration with general practitioners (GPs) in primary care settings in patients with mild-to-moderate mixed anxiety-depressive disorder, in terms of perceived quality of life and general health, compared to usual care, provided by GPs.

The secondary objectives are to assess the effect of the CBT-based psychological intervention on the level of anxiety and depressive symptoms, healthcare costs in terms of consumption of psychoactive drugs and use of healthcare resources, and the sick leave taken (number of times and the length of absence), compared to usual care. Additionally, our aim is also to assess the level of satisfaction of doctors and patients in both groups regarding the treatment administered, twelve months after the beginning of the intervention.

### Study hypotheses

The main working hypothesis is that the CBT delivered by psychologists will be more effective than the usual care provided by primary care doctors, in terms of an improvement by at least 10 points on the Short Form-36 General Health Survey (SF-36) in the mid (6 months) and long (12 months) term in patients with mixed anxiety-depressive disorder.

Additionally, the intervention will be more effective than usual care in the reduction of anxiety and depressive symptoms, as assessed by the State-Trait Anxiety Inventory (STAI) and the Beck Depression Inventory (BDI), respectively.

Further, we expect to observe a greater reduction in healthcare costs in terms of consumption of psychoactive drugs and use of healthcare resources as well as in the number and length of sick leave absences in the intervention group than in the control group.

Finally, we also expect GPs and patients to be more satisfied with the intervention than the control treatment.

## Methods/Design

### Design of the trial

This will be an open-label parallel-group randomised controlled trial. Eligible patients will be randomly assigned to one of the study groups: the intervention group (IG), receiving a CBT-based psychological treatment together with usual care, or the control Group (CG) receiving usual care provided by GPs. The principal outcome measure will be the change in quality of life in patients with mixed anxiety-depressive disorder, assessed at four times points: at baseline, that is, pre-treatment; and at 3, 6 and 12 months after the initial assessment.

### Setting

A total of 41 GPs of 7 primary care health centres will participate in the study. The psychologists in charge of delivering the psychological therapy are staff of the Basque Health Service. Patient assessments will be performed by a researcher contracted for the purpose with specific training for taking the required measurements.

The health centres have the necessary infrastructure and resources to carry out the measurements and the intervention.

### Participants and recruitment process

Eligible subjects will be: patients of the participating health centres, over 18 years of age, who have been diagnosed by their GP with mild-to-moderate mixed anxiety-depressive disorder, and obtained scores of at least 4 on the anxiety subscale and at least 3 on the depression subscale of the Goldberg Anxiety and Depression Scale (GADS) [28,29] (see Figure 1 for an overview). We will apply the following exclusion criteria: being over 75 years old; not being able to understand and/or speak Spanish; or having cognitive impairment that could interfere with assessments or intervention; a serious disease or medical condition that could result in death in the following 12 months or a high probability of loss to follow up; or a psychotic or other severe mental illness, as well as a history of suicide attempts or persistent suicidal ideation. Patients who referred to specialised care and any under psychological treatment in the private sector will also be excluded.

**Figure 1 Fig1:**
[figure not shown]
**Flow chart of patient recruitment and randomisation.**

The study will be presented to the GPs of the participating centres. Among those interested in participating in the study, we will randomly select (using a computer program) a sample of 41 GPs balanced by health centre.

Each participating GP will be given a list of patients based on the search criterion “active mixed anxiety-depressive disorder”. From each list of eligible patients, a sample of six patients we be randomly selected to be given an appointment at which their GP will explain the details of the study and check that patient meets the inclusion criteria. If they do, the patient will be formally invited to participate, giving them a copy of the patient information leaflet and informed consent form.

Once they have signed the informed consent form, participating patients will be randomly assigned to the IG or the CG following a simple randomisation with a 1:1 allocation ratio using the EpiData 4.0 computer program, with the interviewer and the person in charge of data analysis being blind to group allocation at all times.

### Materials

GPs will use the Spanish version of GADS [28,29] for screening their samples of patients. This scale consists on a short interview questionnaire that has been shown to be useful in the identification of likely cases of anxiety and depression. It has good psychometric properties, with a sensitivity and specificity above 80% [29]. Scores of at least 4 on the anxiety subscale and of at least 3 on the depression subscale have been established as an inclusion criterion.

An assessor trained for the purpose, contracted for the project and blind to patient group allocation, will carry out assessments at four time points over course of the study: baseline (pre-treatment) and 3, 6, and 12 months after the intervention. To assess the level of depression, we will use the BDI [30] validated for the Spanish population by Sanz et al. [31]. The BDI has acceptable psychometric properties as an assessment instrument for measuring depressive symptoms in adults, and is the most widely used questionnaire for assessing the response to treatment of patients with depression.

As for assessing the level of anxiety, we will use the Spanish version of the STAI [32,33]. The STAI is a self-administered questionnaire composed of 40 items rated on a 4-point Likert scale. It assesses two independent types of anxiety: anxiety as a trait (A/T), which refers to relatively permanent and stable dimension of personality or a tendency towards reacting anxiously; and anxiety as a state (A/S), which detects behaviours associated with transient situational anxiety, present during the assessment.

For assessing health-related quality of life and general status, we will use the Spanish version of the SF-36 [34,35]. It is composed of 36 items rated on Likert scales and refers to various aspects of health divided into 8 dimensions (physical functioning, role-physical, bodily pain, general health, vitality, social functioning, role-emotional and mental health). In addition, two global subscores can be calculated that represent the physical and mental state of health: the physical component summary (PCS) and the mental component summary (MCS). All the raw scores of the SF-36 are normalised and transformed to a scale from a 0 to 100, with higher scores indicating better general health status and self-perceived quality of life.

Additionally, at the first (baseline) and the last (12 months) assessments, patients will complete the Health Resource Use Questionnaire, prepared *ad hoc* to collect data on the use of healthcare resources in the previous weeks, as well as the use of drugs and medical consultations, among other factors. Finally, in the last assessment (12 months), all the patients and GPs participating in the study will be asked about their level of satisfaction with the treatment provided, rating it on a visual analogue scale (VAS) ranging from 0 to 10.

### Intervention

Patients assigned to the CG will be treated by their GP and will receive the usual care. Patients assigned to the IG will be contacted by telephone by the psychologist to make a first appointment and plan the subsequent sessions. The design of the intervention is based on CBT programmes for groups developed by local experts in the field [36,37]. The research team has updated these programmes and adapted them for use with individuals, with additional information technology support and giving a more active role to patients.

The intervention consists of 8 individual 60-minute face-to-face sessions, to be carried out during 8 consecutive weeks in the health centres. Six months after the start of the intervention, at the same time as the third measurement, there will be a follow-up session over the telephone, for reinforcement or referral, as appropriate.

Each of the sessions has specific objectives and is focused on various areas:1^st^ session: Psychoeducational explanation of the nature and characteristics of mixed anxiety-depressive disorder. Contextualisation of the intervention. Provision of a copy of the patient handbook.2^nd^ session: Establishment of a programme of rewarding or reinforcing factors based on carrying out regular enjoyable activities, to be recorded by patients in their handbook. Training in relaxation and controlled breathing. Sleep hygiene advice.3^rd^ session: Tackling the symptoms of anxiety. Construction of a hierarchy of feared situations, counselling on exposure to stress factors or feared situations.4^th^ session: Learning and developing techniques focused on detecting and blocking automatic negative thoughts5^th^ session: Learning and developing techniques focused on restructuring automatic negative thoughts6^th^ session: Role playing. Work on situations that perceived as difficult. Learning strategies for problem solving. Self-instruction and self-control.7^th^ session: Developing social skills. Assertiveness and self-concept.8^th^ session: Assessment and end of the intervention. Implementation of strategies to prevent relapses.Follow-up session. Telephone consultation lasting for 15 minutes, 6 months after starting the intervention. Identification of high-risk cases; monitoring, reinforcement or referral, as appropriate.

As well as this CBT-based intervention, patients assigned to the IG will also be treated by their GP with the usual care.

### Adverse effects

There is no evidence concerning the potential adverse effects of the CBT-based psychological intervention. However, during the intervention, the psychologist and GP will record any incidents that could be harmful to the patient, regardless of whether there is a causal relationship with the intervention. All the adverse effects will be recorded in a database created for the purpose, stating their severity and causal association with the treatment. Additionally, there will be a committee, independent of the research team that will monitor the safety of the treatment under study and will analyse and extensively review any adverse effects that occur during the study.

### Data quality and management

We have taken various steps to ensure the quality and reliability of the data collected in the study including:Creation a specific case report form, with notes on each caseDouble data entry to minimise errors during data storage and processingPreparation of documents to support health professionals in decision making and to facilitate the standardisation of the intervention and data collection

### Sample size

We have estimated a target sample of 246 patients, equally divided between the IG and the CG. This sample size would provide a statistical power above 80% for detecting a difference between the IG and the CG of at least 10 points in the overall SF-36 score as significant (p < 0.05) using a two-tailed Student’s t-test (standard deviation = 13.15, obtained from previous study with similar populations [1]). Similarly, this sample size would provide a statistical power above 80% for detecting as statistically significant a difference of at least 10 points in scores on the following dimensions: general health, vitality and mental health in the SF-36 health survey (SD = 22.10).

We have estimated a loss to follow-up of 10% during the 12-month follow-up.

### Statistical analyses

The statistical analysis of data will be performed on an intention-to-treat basis, comparing the changes in the two groups, IG and CG, in the measurements taken 3, 6 and 12 after the initial assessment. The effect attributable to the intervention will be assessed by analysing the difference in the changes between the groups, and 95% confidence intervals will be calculated, adjusting the values for the baseline levels, using analysis of covariance (ANCOVA). As the baseline level, results will be adjusted for covariable that could confound or modify the effect of the intervention.

To take into account the potential effect of having patients grouped by GPs, the aforementioned ANCOVA models will be extended to mixed-effect models that include the random effect of each GP, both on the intercept and the effect of the intervention.

Finally, to analyse the overall changes in health-related quality of life over the 12 months of the study, the effect of time on the 4 repeated measures collected from each patient will be estimated using a longitudinal mixed-effect model with fixed effects (intervention, time, time-intervention interaction) and random effects (specific effect of each subject and each doctor and health centre).

Interactions between time and the specific effect of subjects, GPs and health centres will also be explored.

Data analysis will be performed using the statistical package SAS for Windows.

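### Neither mixed model has a psychologist effect in the intervention arm, so intervals will be too narrow if outcomes differ between psychologists who each treat patients of several GPs

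*Protocol article*

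**What the plan says.** Under Statistical analyses, the protocol article allows for patients being grouped by GP. It extends the ANCOVA to "mixed-effect models that include the random effect of each GP, both on the intercept and the effect of the intervention". The longitudinal model has fixed effects for intervention, time and their interaction, and "random effects (specific effect of each subject and each doctor and health centre" among its terms. Interactions of time with subject, GP and centre are to be explored. No model names the psychologist.

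Under Setting: "The psychologists in charge of delivering the psychological therapy are staff of the Basque Health Service". Under Intervention, the therapy is eight individual sessions for the intervention group, while controls see only their GP. Randomisation is by patient, 1:1, with six patients sampled from each of 41 GPs in 7 centres. Neither the number of psychologists, nor their caseload, nor how they are matched to GPs or centres is stated.

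Under Sample size: "We have estimated a target sample of 246 patients, equally divided between the IG and the CG". That section claims more than 80% power to find a 10-point gap on the total SF-36 in a two-sided 5% test, and gives its variability as "standard deviation = 13.15, obtained from previous study with similar populations [1". The same power is claimed for 10 points on three dimensions with SD 22.10. Expected loss to follow-up is 10%.

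**The concern.** Because patients are randomised individually, most GPs will have patients in both arms, so GP and centre intercepts largely cancel from the treatment contrast. A psychologist effect does not cancel, because it exists in one arm only.

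The GP-by-intervention term is a partial substitute. It sees about three intervention patients per GP and treats the 41 GPs as independent. If one psychologist serves several GPs, the intervention effects of those GPs are correlated, and the model does not know it. The longitudinal model has no intervention slope at any level. Its centre effect is shared by both arms, and the interactions to be explored are with time, not with intervention.

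At stake are the width of the interval and the reach of the conclusion. The Discussion looks ahead to health authorities adopting the service, which means other psychologists. Variation between psychologists then belongs in the uncertainty of the estimate.

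**Working it through.** **Inputs from the protocol article.** 123 patients per arm; 10% loss, so n = 0.9 × 123 ≈ 111 per arm; 41 GPs; difference 10 points; SD 13.15 (overall score) or 22.10 (dimensions); two-sided 5%.

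**Assumptions, not in the document.** Number of psychologists K = 4 to 20, ICC = 0 to 0.05, equal caseloads, equal total variance in both arms.

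**Step 1: the plan's own figure.** SE = SD × √(2/n), power = Φ(10/SE − 1.96). At 123 per arm, power is over 0.999 (SD 13.15) and 0.944 (SD 22.10). With 111 per arm it is over 0.999 and 0.92. The claim of more than 80% is reproduced, with room to spare.

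**Step 2: true variance with psychologist clustering.** Design effect in the intervention arm: DE = 1 + (111/K − 1) × ICC. True variance is proportional to DE + 1, because the control arm contributes 1.

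**Step 3: variance that the GP-slope model credits.** With 111/41 ≈ 2.7 intervention patients per GP, this is [1 + 1.7 × ICC] + 1. It applies when psychologists are tied to GPs. If they are crossed with GPs, the term absorbs almost nothing.

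**Step 4: type I error** = 2Φ(−1.96 × √(credited/true)).

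Example, K = 5 and ICC 0.05: DE = 1 + 21.2 × 0.05 = 2.06, so true = 3.06; credited = 1.085 + 1 = 2.085. √(2.085/3.06) = 0.826, and 2Φ(−1.618) = 10.6%. Against an analysis with no clustering at all, the SE ratio is √(3.06/2) = 1.24.

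**Step 5: power.** SE = SD × √((DE + 1)/111). The normal approximation is Φ(10/SE − 1.96). The small-sample version uses the noncentral t distribution with Satterthwaite df = (DE + 1)² / (DE²/(K − 1) + 1/110).

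Example, K = 5, ICC 0.05, SD 22.10: SE = 22.10 × √(3.06/111) = 3.67 and Φ(2.725 − 1.96) = 0.778. df = 9.36/(1.061 + 0.009) ≈ 8.8, and power is about 0.68.

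| K | ICC | DE | Type I error, GP terms | Power SD 13.15 (normal) | Power SD 22.10 (normal) | Power SD 22.10 (small-sample df) |
|---|---|---|---|---|---|---|
| 4 | 0.02 | 1.54 | 7.9% | 0.999 | 0.85 | 0.75 |
| 4 | 0.05 | 2.34 | 12.1% | 0.99 | 0.74 | 0.59 |
| 5 | 0.05 | 2.06 | 10.6% | 0.996 | 0.78 | 0.68 |
| 7 | 0.02 | 1.30 | 6.5% | >0.999 | 0.88 | 0.85 |
| 7 | 0.05 | 1.74 | 8.7% | 0.998 | 0.82 | 0.77 |
| 14 | 0.02 | 1.14 | 5.6% | >0.999 | 0.90 | 0.89 |
| 14 | 0.05 | 1.35 | 6.5% | 0.999 | 0.88 | 0.86 |
| 20 | 0.02 | 1.09 | 5.3% | >0.999 | 0.91 | 0.90 |

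With ICC 0, or K = 41 and one psychologist per GP, type I error is 5.0%. For the overall score at K = 4 and ICC 0.05, small-sample df (about 6.1) still leaves power of about 0.95.

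**Step 6: no GP-by-intervention term, as in the longitudinal model.** The credited variance is then 2, and type I error is 2Φ(−1.96 × √(2/(DE + 1))): 6.7% at K = 7, ICC 0.02 and 12.9% at K = 4, ICC 0.05. This treats the contrast at a single time point.

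**Step 7: check by simulation.** 20,000 trials per setting, 41 GPs with three patients per arm each, GP-level differences tested with 40 df. With one psychologist per centre (K = 7), coverage of the nominal 95% interval was 93% at ICC 0.02 and 91% at ICC 0.05. With one per GP it was 95%.

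**The case against.** The strongest reply is that the size, and even the existence, of the shortfall rests on two unknowns. No section gives the number of psychologists or an ICC. With an ICC of 0, or one psychologist per GP, the stated model is adequate; with 14 to 20 psychologists and ICC 0.02 to 0.05 the test runs at only about 5.3% to 6.5%. This stands. A reader might infer that the intervals are too narrow as a matter of fact, but the document does not support that. It does make one psychologist per GP look unlikely, since that would take 41 psychologists and the Limitations section doubts that enough can be recruited.

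Second, the plan already does more than many: it lets the intervention effect vary by GP, and it fixes the content of each session and supplies documents to standardise delivery. These measures may lower the ICC, and the GP slope takes up some of the variance when psychologists are tied to GPs. They do not replace a term for an effect shared across GPs.

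Third, a reader might infer that the trial is underpowered. It is not for the overall SF-36, on which it is first sized.

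Fourth, an analysis plan that is not shown could add the term. However, the article writes its random effects out level by level, so the comment is on a stated model and not on a missing detail.

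**Conclusion.** The point holds in conditional form. The stated models omit a clustering level that exists in the intervention arm only. Any positive psychologist ICC shared across GPs makes the interval for the intervention effect too narrow.

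Over K = 4 to 20 and ICC 0 to 0.05, the nominal 5% test with the GP terms runs at about 5% to 12%. Fewer psychologists or a larger ICC would make it worse. The power claim for the overall score (SD 13.15) survives over this range. The claim for the dimensions (SD 22.10) is the exposed one: at K = 4 to 5 and ICC 0.05 it falls to about 74-78% by normal approximation, or 59-68% with small-sample df.

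Because both K and the ICC are assumed and the overall-score power is intact, this is a should-fix and not a must-fix point.

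**What to change.** Record the treating psychologist for every intervention patient from the start; without this identifier the problem may not be repairable later. Prespecify a partially nested version of the ANCOVA and longitudinal models, with a random psychologist effect in the intervention arm only (each control patient as their own cluster) and Satterthwaite or Kenward-Roger degrees of freedom. It should be at least a sensitivity analysis. State the number of psychologists expected, and give the power for the dimensions over a range of assumed ICC.

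The cost is one identifier and a few lines of text. The downside is a wider interval and, if psychologists are few, an imprecisely estimated variance component with few degrees of freedom. The loss of stated power is then not slight: at K = 5 and ICC 0.05, the small-sample correction alone takes the dimension power from about 78% to about 68%. That is a reason to accept a sensitivity analysis in place of a mandatory primary model.

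### The supplementary longitudinal model leaves the arms free to differ at baseline, so its intervention-by-time estimates are unbiased but less precise than the baseline-adjusted ANCOVA planned beside it

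*Protocol article*

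**What the plan says.** The Statistical analyses section of the protocol article describes three steps.

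1. The intervention effect is assessed as the between-group difference in change, "adjusting the values for the baseline levels, using analysis of covariance (ANCOVA").
2. To allow for patients being grouped by doctor, "the aforementioned ANCOVA models will be extended to mixed-effect models that include the random effect of each GP". The baseline adjustment carries over.
3. Last, "to analyse the overall changes in health-related quality of life over the 12 months of the study", a longitudinal model estimates "the effect of time on the 4 repeated measures collected from each patient". It is a "longitudinal mixed-effect model with fixed effects (intervention, time, time-intervention interaction") and has "random effects (specific effect of each subject and each doctor and health centre").

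The Design of the trial section fixes the four occasions: "at baseline, that is, pre-treatment; and at 3, 6 and 12 months after the initial assessment". Baseline is therefore one of the four outcomes in step 3. The listed fixed effects include neither a baseline covariate nor a constraint of equal baseline means.

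**The concern.** Patients are randomised individually, 1:1, so the arms have the same expected baseline mean. In the step 3 model with categorical time and baseline as the reference visit, the intervention main effect is the baseline difference between arms, which is chance alone. Each interaction term is then the raw difference between arms in mean change from baseline. The model spends information on a quantity known in expectation to be zero, and it gives up the regression adjustment that the same section chose for the ANCOVA.

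Two things are at stake. The intervention-by-time estimates from this model are less precise than the same data allow. In addition, the main hypothesis concerns 6 and 12 months, and both analyses yield estimates at those visits. They can give visibly different numbers from the same patients only because the arms happened to differ at baseline.

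**Working it through.** **Inputs from the protocol article (Sample size).** "We have estimated a target sample of 246 patients, equally divided between the IG and the CG", so 123 per arm. Loss to follow-up is 10%: 0.9 × 123 = 110.7, taken as 110 per arm. The target difference is 10 points, two-sided 5% level. The SD is 13.15 (overall SF-36 score) or 22.10 (general health, vitality and mental health).

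**Assumptions not in the article.** The baseline/follow-up correlation r is not given, so a range is shown. Time is categorical, the SD is the same at each visit, all pairs of visits have the same correlation (as a random subject intercept implies), data are complete, and GP and centre effects are ignored.

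**The plan's own figure.** By the normal approximation to the two-sample comparison, 123 per arm gives power of 94.4% at SD 22.10 and above 99.9% at SD 13.15. With 110 per arm the figures are 91.9% and 99.99%. The stated power of more than 80% is reproduced as a lower bound.

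**Variance of the effect at one visit, n per arm.**

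- Listed longitudinal model (difference in change): 2·SD²·(1−r)·(2/n)
- Baseline-adjusted (ANCOVA or common baseline mean): SD²·(1−r²)·(2/n)
- Ratio: 2(1−r)/[(1−r)(1+r)] = 2/(1+r)

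**Results at SD 22.10, 110 per arm, 12-month effect.**

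| r | SE, listed model | SE, baseline-adjusted | Variance ratio | Power for 10 points, listed | Power, adjusted |
|---|---|---|---|---|---|
| 0.3 | 3.53 | 2.84 | 1.54 | 81.0% | 94.0% |
| 0.4 | 3.26 | 2.73 | 1.43 | 86.5% | 95.6% |
| 0.5 | 2.98 | 2.58 | 1.33 | 91.9% | 97.2% |
| 0.6 | 2.67 | 2.38 | 1.25 | 96.3% | 98.7% |
| 0.7 | 2.31 | 2.13 | 1.18 | 99.1% | 99.7% |

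Exact generalised least squares on all four visits gives the same standard errors, with the common-baseline model matching the ANCOVA formula. At SD 13.15 power is at least 99.7% under either model for r of 0.3 or more.

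**Bias.** In 4,000 simulated trials at each of r = 0.3, 0.5 and 0.7 with a true effect of 10, both estimators averaged 10.0.

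**Disagreement in one trial.** The two estimates differ by (1−b) times the observed baseline difference, where b is the fitted ANCOVA slope, close to r. The baseline difference has SD 22.10·√(2/110) = 2.98 points, so the gap has SD:

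- r = 0.4: 0.6 × 2.98 = 1.8 points
- r = 0.5: 0.5 × 2.98 = 1.5 points
- r = 0.7: 0.3 × 2.98 = 0.9 points

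In one simulated trial (r = 0.5) with a 4.7-point baseline difference, the listed model gave 5.1 and the ANCOVA 7.0. In further simulation the two fell on opposite sides of p = 0.05 in about 20% of trials at r = 0.4 and 13% at r = 0.7 for a true effect of 5 points. For a true effect of 10 points the figures were about 10% and 1%.

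**Dependence on categorical time.** If time is linear (0, 3, 6, 12 months), a common baseline mean still lowers the variance of the 12-month effect, by 28% at r = 0.4 and 12% at r = 0.7. With categorical time the reductions are 30% and 15%.

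**The case against.** The strongest reply is that the plan already estimates the intervention effect properly. The ANCOVA and its GP extension are named for that purpose, and the longitudinal model comes last, to describe change over the year. Group, time and their interaction form a standard and valid model. Its contrasts do account for baseline by subtraction, and at the article's own SDs power stays above 80% for r of 0.3 or more. Neither r nor the coding of time is stated, and an explicit order of precedence is the kind of detail an article leaves to a fuller document.

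Most of this stands, and it rules out two stronger readings. A reader might infer that the plan abandons baseline adjustment. It does not, since the first two steps of the section keep it. A reader might also infer that the two analyses target different effects or that one is biased. Under randomisation both are unbiased for the same effect, and the gap in any one trial comes from chance imbalance.

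The reply does not remove the efficiency point. The outcome occasions and the fixed effects are stated, not left open, and a model fitted as listed gives less precise intervention-by-time estimates than the same data would support. Because the interaction is in the model, those estimates will exist beside the ANCOVA results.

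**Conclusion.** The point holds as a modest improvement in efficiency and consistency, confined to the supplementary longitudinal model. As listed, its intervention-by-time contrasts have variance about 43% to 18% higher than a baseline-adjusted estimate for r of 0.4 to 0.7, which is a standard error about 20% to 8% larger (√1.43 = 1.20; √1.18 = 1.08). The size depends on the assumed r, on categorical time, on equal SDs across visits, on complete data and on ignoring clustering.

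The documents do not support calling it a failed power claim. The trial was sized on an unadjusted t-test, and the power above 80% holds under either model for r of 0.3 or more.

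**What to change.** In the longitudinal model, keep all four measures, make time categorical, and remove the intervention main effect so that both arms share one baseline mean. The interaction must then be coded for the 3-, 6- and 12-month visits only, for example by giving every patient the control code at baseline. Merely deleting the main effect from a SAS model with class variables leaves the interaction free at baseline and imposes no constraint. Alternatively, model the 3-, 6- and 12-month values as outcomes with baseline as a covariate interacting with time.

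Keep the ANCOVA mixed model as the analysis of the intervention effect, and say so in a sentence so that its precedence is explicit. Both the common baseline mean and the ANCOVA presume that the baseline assessment is unaffected by knowledge of allocation, so the revised text should confirm this.

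The cost is one changed model line and a sentence of text. No extra data or patients are needed, since baseline is already collected.
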